## Methods

### Study Aim

The primary aim of our study is to assess the long-term health effects of RRSO on subclinical CVD, bone mineral density (BMD), and cognitive functioning in women at increased familial risk of breast or ovarian cancer mainly due to a *BRCA1/2* mutation. Our secondary study aims are to assess overall HRQoL, endocrine symptoms, such as hot flashes and night sweats, sexual functioning, urogenital problems, and the prevalence of cardiovascular risk factors.

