### Recruitment

We will include 500 women who have undergone RRSO before the age of 45 years, with a follow-up period of at least 10 years (the early RRSO group). We will compare them with 250 women from the same cohort (frequency matched on current age) who have not undergone preventive RRSO or have undergone RRSO at the age of 55 years or above (the late/non-RRSO group). The exclusion criteria are a metastatic disease; a serious physical comorbidity or psychiatric disorder; a language barrier; a metal cardiac valve; a bare metal coronary stent, since the reflection of the stent would interfere with the computed tomography scan; and natural POI before the age of 40 years. A history of nonovarian cancer, including breast cancer, is not a reason to be excluded.

Eligible women who are alive will be invited for a clinic visit and questionnaire survey that will assess CVD status, BMD, cognitive functioning, and HRQoL. For eligible women who have died, we will collect information on the causes of death to examine selection bias.

Participants will be selected from the dynamic nationwide HEBON study cohort, a national collaboration on HEreditary Breast and Ovarian cancer in the Netherlands, with women tested for *BRCA1/2* germline mutations included since 1997 by all eight Dutch University Medical Centers (UMCs) and the Netherlands Cancer Institute (NKI). The cohort currently consists of over 3600 proven female *BRCA1/*2 germline mutation carriers. Participants have given informed consent for linkage with the Netherlands Cancer Registry and the Dutch Nationwide Pathology Database (PALGA), which can provide information on all prophylactic mastectomies and salpingo-oophorectomies performed in the Netherlands since 1991. This provides us with nearly complete information on the occurrence of RRSO. Data on lifestyle, family history, reproductive factors, and hormone use have been collected from HEBON participants through questionnaires [44].

Figure 2 provides a schematic overview of the patient selection and eligibility criteria of our study population.

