### Sample Size Calculation

We based our sample size calculations for cardiovascular status on subclinical atherosclerosis by assessing the differences in the CAC score between women in the early RRSO group and women in the late/non-RRSO group. We chose a clinically relevant cutoff for the CAC score of 100 Agatston units (AU). According to the MESA trial, 10% of subjects between 55 and 65 years of age exceed this value [78]. For sample size estimation, we hypothesized that 20% of the early RRSO group exceeds this value of 100 AU. In logistic regression with an elevated CAC score (>100) as the outcome and with 250 women in the late/non-RRSO group and 500 women in the early RRSO group, we have 80% power to detect an odds ratio of 1.9 at an α value of 5%.

With 750 women in our study, we will be able to detect a difference of 0.07 g/cm^2^ in BMD between the early RRSO and late/non-RRSO groups, as observed between women with premature and normal menopause and assuming an SD of 0.15 [79]. Statistical power for analysis of cognitive functioning is based on a previous neuropsychological study on the effects of oophorectomy on cognitive impairment and dementia [34]. This study reports relevant differences in 427 women with bilateral oophorectomy before the age of 49 years, compared to age-matched women without oophorectomy, with a median follow‐up of 25 years. As our neurocognitive tests are more sensitive than the tests screening for dementia, we expect to be able to detect smaller differences in cognitive functioning and distinguish between different cognitive domains, and with 750 participants, we have 90% power to detect an effect size of 0.25 with a *P* value set at .05 (two tailed). To detect a relevant difference between groups for the various HRQoL measures, we will use a half SD (an effect size of 0.5) to define clinically relevant group differences (over time). This requires about 67 patients per group. The available sample will be more than adequate to conduct subgroup analyses as well.

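### The coronary stent exclusion removes women from the whole study for a CT-only reason and selects on the cardiovascular outcome, so it can bias the CAC comparison in a direction the documents do not settle

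*Protocol article*

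**What the plan says.** The Recruitment section of the protocol article gives one list of criteria for the whole study: "The exclusion criteria are a metastatic disease; a serious physical comorbidity or psychiatric disorder; a language barrier; a metal cardiac valve", then "a bare metal coronary stent, since the reflection of the stent would interfere with the computed tomography scan", and natural POI before age 40. The CT reason is attached to the stent; none is given for the valve. No exception is made for the parts of the study that do not use CT.

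Under Study Aim, the cardiovascular part is worded as follows: "The primary aim of our study is to assess the long-term health effects of RRSO on subclinical CVD". Bone mineral density and cognitive functioning stand beside it as primary aims.

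The Sample Size Calculation uses CAC above 100 Agatston units as the cardiovascular endpoint. It takes from a reference cohort that "10% of subjects between 55 and 65 years of age exceed this value" and claims 80% power for an odds ratio of 1.9 at α 5%, "with 250 women in the late/non-RRSO group and 500 women in the early RRSO group".

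On selection, Recruitment plans to collect causes of death for eligible women who have died. The Discussion names survivor bias as a limitation and says in general terms that comparison with the entire cohort will quantify survivorship and selection bias.

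**The concern.** Two things are wrong with the stent rule.

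First, a problem with one measurement is used to remove a woman from all of them. Metal artefact has no bearing on DXA of spine and hip, the online cognition scan, pulse wave velocity, skin autofluorescence, blood markers or questionnaires. The same article handles a parallel problem differently: β-CTX is invalid in nonfasting blood, so that marker is dropped for nonfasting women and the women stay in the study.

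Second, the rule is related to the outcome and acts after exposure. A stent is placed for established coronary disease, the condition for which CAC is the surrogate. Early RRSO women are seen at least 10 years after surgery, so some stents may postdate RRSO. Excluding these women takes cases from the severe end of the one cardiovascular endpoint that has a power calculation. A distorted contrast would matter here: the Introduction and Discussion both say that finding no raised CVD risk would fit the view that early menopause is not itself the cause, so a null result would be interpreted.

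The deaths-only check cannot recover living women turned away for a stent. The linkages named in Recruitment (cancer registry and pathology database) are not described as supplying cardiac history.

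**Working it through.** **Inputs from the Sample Size Calculation.** Reference rate of CAC >100: p0 = 0.10. Detectable OR: 1.9. Group sizes: 250 late/non-RRSO and 500 early RRSO. α = 5%, taken as two-sided because sidedness is not stated for CAC.

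**Step 1: reproduce the plan's figure.** OR 1.9 on a 10% reference gives p1 = 1.9 × 0.10 / (0.90 + 1.9 × 0.10) = 0.19/1.09 = 0.1743. Two-proportion power at 250/500 is 78.6%, close to the stated 80%.

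**Step 2: effect of the exclusion.** Let s0 and s1 be the shares of the control and early RRSO groups that are excluded. Assume every excluded woman would have had CAC >100. The rate among the remaining women is (p − s)/(1 − s), and the odds are (p − s)/(1 − p). Therefore

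OR observed = 1.9 × (1 − s1/p1) / (1 − s0/p0).

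The OR falls below 1.9 only if s1/p1 > s0/p0, that is, if s1/s0 > p1/p0 = 0.1743/0.10 = 1.74. A higher excluded share in early RRSO is not enough; it must be more than about 1.74 times the control share.

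**Step 3: scenarios.** The documents give no stent or valve prevalence, so s0 and s1 are assumptions. Analysed group sizes are held at 250 and 500.

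| Excluded, controls / early RRSO | Rates observed | OR | Power |
|---|---|---|---|
| none | 10.0% / 17.4% | 1.90 | 79% |
| 0.5% / 1% | 9.5% / 16.6% | 1.89 | 76% |
| 1% / 1% | 9.1% / 16.6% | 1.99 | 82% |
| 1% / 1.5% | 9.1% / 16.2% | 1.93 | 77% |
| 1% / 3% | 9.1% / 14.9% | 1.75 | 61% |
| 2% / 2% | 8.2% / 15.7% | 2.10 | 85% |
| 2% / 3% | 8.2% / 14.9% | 1.97 | 76% |
| 2% / 4% | 8.2% / 14.0% | 1.83 | 65% |

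Worked rows: for 1%/3%, (0.1443/0.8257)/(0.09/0.90) = 1.75; for 1%/1%, (0.1643/0.8257)/(0.09/0.90) = 1.99.

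If the same fraction of CAC >100 women is lost in each group, for example 10% of them, the OR stays at 1.90. The risk difference shrinks from 7.4 to 6.9 points and power is 75%.

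**Step 4: the plan's other assumption.** The article also states "we hypothesized that 20% of the early RRSO group exceeds this value of 100 AU". At 10% versus 20% the OR is (0.20/0.80)/(0.10/0.90) = 2.25, power is 95%, and the break-even ratio is 2. Exclusions of 1%/3% then give OR 2.13 and power 89%; 2%/2% gives OR 2.53.

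**The case against.** A reader might infer that the exclusions bias the CAC comparison toward the null. The documents do not support this. Losing more treated coronary disease after early RRSO is plausible under the study's own hypothesis, but the OR falls only beyond the 1.74 ratio. With 50% more exclusions in early RRSO (1%/1.5% or 2%/3%) it moves away from the null. The low-power scenarios rest wholly on assumed prevalences.

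A reader might also take the rule to cover all coronary stents, any revascularisation or prior CVD in general. The text says bare metal stent. Bypass surgery and prior infarction are not listed, and the questionnaire asks about cardiovascular history, which suggests that women with prior CVD can take part. Nor is a metal valve the coronary outcome. The criterion "a serious physical comorbidity or psychiatric disorder" is undefined in this condensed article, any link to CAC is indirect, and its definition may stand in the full protocol.

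The stated aim is subclinical CVD, so leaving clinically treated coronary disease out of the CAC analysis partly fits it. This argument stands against making a composite of CAC and stent the main endpoint. It does not explain exclusion from bone, cognition and quality of life, and the Discussion also promises insight into the prevalence and severity of CVD.

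Finally, the Discussion's undertaking to quantify selection bias is not limited to deaths. That is fair, but it is general and names no check for living women excluded by these criteria.

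**Conclusion.** The point holds as a design weakness of unknown direction and probably limited size. The criteria are study-wide, the only reason given concerns one test, and the stent criterion is related to the cardiovascular outcome and can act after exposure. It can therefore bias the CAC >100 comparison. Whether the OR is lowered or raised depends on the excluded shares, which the documents do not give: across the tabulated assumptions it runs from 1.75 to 2.10 around a true 1.90. These figures assume that every excluded woman has CAC >100 and that group sizes are held at target. If stents are rare, as in the 0.5%/1% case (OR 1.89, power 76%), little changes. The unnecessary loss of these women from the bone, cognition and quality-of-life assessments does not depend on any of these assumptions. The change is worth making because recruitment is still open (364 of 750 enrolled in November 2020).

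**What to change.** - Limit the bare metal stent and metal valve criteria to the CT measurement. Keep these women in DXA, cognition, pulse wave velocity, AGEs, blood sampling and questionnaires.
- Keep measured CAC >100 as the main analysis, in line with the subclinical aim.
- Add a sensitivity analysis that counts women with a coronary stent as CAC >100.
- Tabulate, by group and reason, the women excluded and the participants without a CT, including those turned away before the change. This supplies the shares needed to judge direction and size.

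The cost is a small eligibility amendment, one coding rule for the sensitivity analysis, and a few participants without a CAC score.

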**Figure 2 figure2:**
[figure not shown]
Schematic overview of the eligibility criteria.

Participants will be asked to complete an online questionnaire and an online cognitive assessment, and they will be asked to visit the outpatient clinic for a cardiovascular and bone health assessment. We will assess several surrogate endpoints of cardiovascular health, that is, coronary artery calcium (CAC) score (CAC scoring), pulse wave velocity (PWV), advanced glycation end products (AGEs), anthropometric measurements, and blood sampling. We will determine nonfasting blood levels of lipids, glucose, HbA_1c_, high-sensitivity cardiac troponin, and high‐sensitivity C‐reactive protein. BMD is assessed by a dual-energy X-ray absorptiometry (DXA) scan and laboratory blood sampling, and cognitive functioning is assessed by the Amsterdam cognition scan (ACS).

The online questionnaire is divided into the following several topics: general cardiovascular history, family history of CVD, traditional CVD risk factors (ie, diabetes, hypertension, and cholesterol), lifestyle (ie, smoking, alcohol use, and physical activity), female-specific risk factors (hypertensive pregnancy complications, gestational diabetes, contraceptives use, and HRT use, ie, type, duration, and timing), history of fractures, calcium intake, vitamin D supplement use, glucocorticoid use, family history of osteoporosis/fractures, history of inflammatory diseases (rheumatoid disease and thyroid disorders), and perceived cognitive problems. We will assess generic HRQoL with the SF-36 health survey [45,46] and the body image items of the European Organization for Research and Treatment of Cancer (EORTC) QLQ-BR23 [47,48]. Cancer worries will be measured with the eight items adapted from Lerman et al [49-51]. To assess menopausal symptoms, we will employ the 18-item Functional Assessment of Cancer Therapy-Endocrine Subscale (FACT-ES) and the Hot Flush Rating Scale (HFRS) [52,53]. To assess urogenital problems, the Urogenital Distress Inventory (UDI-6) and Incontinence Impact Questionnaire (IIQ-7) [54] will be used. The Sexual Activity Questionnaire (SAQ) [55] will be used to assess sexual functioning. For patients with a breast cancer history, either before or after RRSO, we will collect information on radiotherapy (yes/no and radiation fields), chemotherapy and immunotherapy regimens, and endocrine treatment from medical records.

Measurements of the CAC score as calculated by coronary calcium scoring will be performed according to standardized local protocols at the various UMCs using the Agatston score (AS) and the Multi-Ethnic Study of Atherosclerosis (MESA) coronary heart disease risk score calculator [56,57]. A disadvantage of CAC scoring might be the use of ionizing radiation. However, the radiation dose in the CAC protocol is as low as 1 mSv, which is not expected to be harmful [58]. All patients in our study are aged 55 years or above; thus, the radiation-induced risk of breast cancer from CAC scoring will be negligible with the current protocol [59,60].

The PWV will be assessed with an ambulatory arteriograph (TensioMed Kft) by the research physician. The arteriograph uses an oscillometric occlusive method, with an upper arm cuff to measure the time interval between the peak of the first systolic wave and the peak of the reflected systolic wave (return time). The device has been validated in numerous studies [61-65].

With aging, the end products of nonenzymatic modification of proteins, lipids, and nucleic acids (AGEs) accumulate endogenously in the serum and tissues. Levels of AGEs in the skin are measured noninvasively by standardized autofluorescence and can predict future cardiovascular events [66,67]. Skin autofluorescence is a quick and noninvasive surrogate marker of tissue accumulation of AGEs [68-70]. AGEs will be measured using the AGE Reader (DiagnOptics Technologies BV; software V 2.3.0.7) on the forearm.

Bone health will be assessed by a DXA scan, a vertebral fracture assessment, and blood levels of bone turnover markers (BTMs) for osteoclast and osteoblast activity (beta-carboxy-terminal collagen crosslinks [β-CTX] and N-terminal procollagen type 1 [P1NP]). For logistic reasons, it is not possible to get fasting blood samples for every woman. Since β-CTX values are only valid in fasting blood samples, we will assess this BTM only in those women for whom we have fasting blood samples. P1NP will be measured in all samples.

Lastly, women will receive an invitation to fill out the online ACS, which has recently been developed and validated [71]. The ACS is an easy to use tool to obtain online measures of various cognitive abilities [72]. The online test battery is based on seven traditional neuropsychological tests and covers the following domains: verbal memory, attention, executive functioning, information processing speed, and motor functioning.

Table 1 provides an overview of the tests that will be performed [58,61-63,66,67,69,71-77]. Table 2 provides an overview of the questionnaires used [45-50,52-55].

We will examine the effect of age at RRSO on the risk of breast cancer, contralateral breast cancer, and ovarian cancer, as well as associations between RRSO and the prognosis of subsequent breast cancer and ovarian cancer. Additionally, after completion of the cross-sectional study, we will perform longitudinal follow-up every 4 to 5 years to evaluate incidence rates of outcomes of major interest, such as ischemic heart disease, and evaluate changes in outcomes (CAC, PWV, BMD, and cognitive functioning as assessed by the ACS) over time between the early RRSO group and the late/non-RRSO group. Moreover, with the anticipated prospective follow-up of our study population, we will look at mortality of cardiovascular disease.

All data, including blood and DNA samples, will be stored for 30 years to enable prospective longitudinal follow-up of the study population on the long-term health effects of RRSO. The stored blood samples will allow for future international studies, for example, those on the modifying effects of genetic factors, such as single nucleotide polymorphisms, on the outcomes of interest, and the novel cardiovascular markers or BTMs for these outcomes. All blood samples will be frozen and stored at −80°C at the NKI.

**Table 1 table1:** Overview of the tests that will be performed.

Aim of the test	Data collection method and references	Outcome variables	Justification
Cardiovascular health	Coronary artery calcium (CAC) scoring [58,73]	Score according to Agatston	Measurements of the CAC score as calculated by coronary calcium scoring will be performed according to standardized local protocols at the various University Medical Centers using the Agatston score (AS) and the MESA^a^ coronary heart disease risk score calculator.
Cardiovascular health	Pulse wave velocity (PWV) [61-63]	In meters/second	The PWV will be assessed with an ambulatory arteriograph (TensioMed Kft) by the research physician. The arteriograph uses an oscillometric occlusive method, with an upper arm cuff to measure the time interval between the peak of the first systolic wave and the peak of the reflected systolic wave (return time).
Cardiovascular health	Advanced glycation end products (AGEs) [66,67,69]	In arbitrary units (AU)	With aging, the end products of nonenzymatic modification of proteins, lipids, and nucleic acids (AGEs) accumulate endogenously in the serum and tissues. Levels of AGEs in the skin are measured noninvasively by standardized autofluorescence and can predict future cardiovascular events. AGEs will be measured using the AGE Reader (DiagnOptics Technologies BV; software V 2.3.0.7).
Cardiovascular health	Anthropometric measurements	Blood pressure in mmHg Pulse frequency per minute Waist (in cm)/hip (in cm) ratio BMI in kg/m^2^	Predictors of future cardiovascular events.
Cardiovascular health	Laboratory blood sampling	Nonfasting blood levels for lipids (total cholesterol, high-density lipoprotein cholesterol, low-density lipoprotein cholesterol, and triglycerides), glucose, HbA_1c_, high-sensitivity cardiac troponin, high‐sensitivity C‐reactive protein	Predictors of future cardiovascular events.
Bone health	Dual-energy X-ray absorptiometry (DXA) scan of the lumbar spine and hip	BMD^b^ values in g/cm^2^ T and Z scores Presence of osteopenia (defined as T-scores of −1 to −2.5) Presence of osteoporosis (defined as T-scores of ≥−2.5)	The DXA scan is most widely used in clinical practice to screen for osteoporosis and is regarded as the “gold standard.”
Bone health	Vertebral fracture assessment (VFA)	Vertebral height reduction in percentage Presence of clinical and nonclinical vertebral fractures	There is a strong additive value of VFA compared with DXA alone [74-76].
Bone health	Laboratory blood sampling [77]	Bone formation by P1NP^c^, mean value in ng/mL Bone resorption by β-CTX^d^, mean value in pg/mL Level of 25-hydroxyvitamin D in the serum in nmol/L	Bone turnover markers (BTMs) for osteoclast and osteoblast activity (β-CTX and P1NP). For logistic reasons, it is not possible to get fasting blood samples for every woman. Since β-CTX values are only valid in fasting blood samples, we will assess this BTM only in those women for whom we have fasting blood samples. P1NP will be measured in all samples.
Cognitive functioning	Amsterdam cognition scan (ACS) [71]	Verbal memory Attention Executive functioning Information processing speed Motor functioning	The ACS is an easy-to-use tool to obtain online measures of various cognitive abilities [72]. The online test battery is based on seven traditional neuropsychological tests.

^a^MESA: Multi-Ethnic Study of Atherosclerosis.

^b^BMD: bone mineral density.

^c^P1NP: N-terminal procollagen type 1.

^d^β-CTX: beta-carboxy-terminal collagen crosslinks.

**Table 2 table2:** Overview of the questionnaires.

Aim of the questionnaire	Topics
Cardiovascular health	General cardiovascular history Cardiovascular disease risk factors (ie, obesity, diabetes, hypertension, and dyslipidemia) Lifestyle (ie, smoking, alcohol use, and physical activity) Female-specific risk factors (ie, hypertensive pregnancy complications, gestational diabetes, contraceptive use, and hormone replacement therapy use) Nontraditional risk factors (history of inflammatory diseases, ie, rheumatoid disease)
Bone health	History of fractures Calcium intake Vitamin D supplements Glucocorticoid use Family history of osteoporosis/fractures History of inflammatory diseases (ie, rheumatoid disease and thyroid disorders)
Cognitive health	Perceived cognitive problems
Health-related quality of life [45-50,52-55]	SF-36 health survey Body image items of the European Organization for Research and Treatment of Cancer (EORTC) QLQ-BR23 Cancer worries; eight items adapted from Lerman et al The 18-item Functional Assessment of Cancer Therapy-Endocrine Subscale (FACT-ES) measure of endocrine symptoms Hot Flush Rating Scale (HFRS) Urogenital Distress Inventory (UDI-6) Incontinence Impact Questionnaire (IIQ-7) Sexual Activity Questionnaire (SAQ)

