**Figure 1 figure1:**
[figure not shown]
Overview of the effects of reduced estrogen levels on various organ systems.

A recent Cochrane systematic review on the benefits and harms of RRSO in women with a *BRCA1/2* mutation stated that no conclusions can be drawn regarding bone fracture incidence and HRQoL, and that further research is needed. CVD and cognition were not included as outcomes in this review, probably because of the paucity of studies [43]. Therefore, the aim of the HARMOny study (Health After eaRly Menopause due to Oophorectomy) is to investigate the long-term health effects of RRSO. We will conduct a cross-sectional study with prospective follow-up nested in a large Dutch cohort. We hypothesize that women with surgically induced premature menopause are at higher risk of subclinical CVD, compromised bone health and osteoporosis, reduced HRQoL, and impaired cognitive functioning, compared to age-matched women with natural menopause after the age of 50 years. Depending on the results, this may lead to active surveillance of the above health problems to improve long-term health and HRQoL in women who have undergone early RRSO.

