### Statistical Analysis

We will analyze differences in the cardiovascular risk profile, BMD, and neurocognitive functioning between the early RRSO group and the late/non-RRSO group using multivariable linear regression analyses and logistic regression analyses with clinically relevant cutoff points for the outcomes of interest. The analyses will be adjusted for confounders, including lifestyle, reproductive factors, and medication use, where applicable. For the analysis of patient-reported outcomes, such as HRQoL, sexual functioning, and menopausal symptoms, we will use mixed effect models.

We expect approximately 40% of the women to have a breast cancer history and will perform the analyses separately in women with and those without a breast cancer history, as breast cancer treatment may affect outcomes. Additional subgroup analyses will be performed according to HRT use (yes/no), *BRCA1/2* mutation status, age at RRSO (<40 years/≥40 years), and time since RRSO (10-15 years/>15 years).

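### Table 1 defines osteoporosis with the inequality the wrong way round (T-score at or above −2.5), so the binary bone outcome as written is the complement of the one intended

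*Protocol article*

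**What the plan says.** Table 1 of the protocol article (Methods) lists the outcome variables from the DXA scan of the lumbar spine and hip: BMD in g/cm², T and Z scores, and two binary categories. The first category is "Presence of osteopenia (defined as T-scores of −1 to −2.5"; the second is "Presence of osteoporosis (defined as T-scores of ≥−2.5". No other place in the article defines either term.

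Three other places bear on how the definition is used:

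- The hypothesis at the end of the Introduction expects a higher risk in women with surgical premature menopause of "subclinical CVD, compromised bone health and osteoporosis, reduced HRQoL, and impaired cognitive functioning". The Study Aim section puts BMD in the primary aim.
- The Statistical Analysis section compares the groups on cardiovascular profile, BMD and neurocognitive functioning by linear regression and by "logistic regression analyses with clinically relevant cutoff points for the outcomes of interest".
- The Sample Size Calculation section treats BMD as continuous: "we will be able to detect a difference of 0.07 g/cm^2^ in BMD between the early RRSO and late/non-RRSO groups", "assuming an SD of 0.15".

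**The concern.** The two categories in one table cell contradict each other. The osteopenia range shows that bone status worsens as the T-score falls from −1 towards −2.5, so the more severe category has to lie beyond −2.5. The printed rule points the other way. It labels normal and osteopenic women as osteoporotic and gives the women with the lowest density no category at all.

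BMD is part of the primary aim, and osteoporosis is named in the hypothesis. The closing paragraph of the Discussion says the study will report on how common and how severe osteoporosis is after RRSO, for use in counselling and decision support. Table 1 is the only source of bone cutoffs for the planned logistic regression. Coded as printed, both the prevalence and the direction of the group effect would be wrong, and an adverse effect of early RRSO would be reported as a benefit.

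**Working it through.** No sample size, power or alpha in the article rests on this cutoff, so there is no planned figure to reproduce. The check is a logical one, followed by two illustrations.

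**1. Classify example T-scores under the rules as written and with the direction reversed.**

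| T-score | Osteopenia (−2.5 to −1) | Osteoporosis as written (T ≥ −2.5) | Direction reversed (T ≤ −2.5) |
|---|---|---|---|
| 0 | no | yes | no |
| −1.5 | yes | yes | no |
| −2.4 | yes | yes | no |
| −2.5 | yes | yes | yes |
| −2.6 | no | no | yes |
| −3.5 | no | no | yes |

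As written, every osteopenic woman is also osteoporotic, every normal woman is osteoporotic, and women below −2.5 fall in neither category. With the direction reversed, the categories are disjoint except at exactly −2.5, where the osteopenia range still touches the cutoff.

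**2. Effect on the logistic regression.** Apart from women at exactly −2.5, who are cases under both rules, the written rule is the complement of the reversed one. Replacing an outcome Y by 1 − Y changes the sign of every logistic coefficient, adjusted or not, so each odds ratio becomes its reciprocal whatever the prevalence.

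**3. Illustration with assumed prevalences** (the article gives none): 10% in the late/non-RRSO group and 18% in the early RRSO group.

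- Direction reversed: (0.18/0.82) / (0.10/0.90) = 1.98.
- As written: (0.82/0.18) / (0.90/0.10) = 0.51.

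**4. Illustration over a range, with an assumed normal T-score and SD 1.** The share classed as osteoporotic is 1 − Φ(−2.5 − mean) as written and Φ(−2.5 − mean) when reversed.

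| Assumed mean T | As written | Reversed |
|---|---|---|
| 0 | 99.4% | 0.6% |
| −1 | 93.3% | 6.7% |
| −1.5 | 84.1% | 15.9% |
| −2 | 69.1% | 30.9% |

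For a group difference, take the article's 0.07 g/cm² over its SD of 0.15, which is 0.47 SD, and treat it as a shift in T-score units (a further assumption).

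- Control mean −1, early RRSO mean −1.47: 6.7% against 15.2%, odds ratio 2.49; as written 0.40.
- Control mean −1.5, early RRSO mean −1.97: 15.9% against 29.8%, odds ratio 2.25; as written 0.44.

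**5. Is the continuous BMD analysis touched?** The sample-size section plans "with 250 women in the late/non-RRSO group and 500 women in the early RRSO group". The standardised difference is 0.07/0.15 = 0.467 and its standard error is √(1/250 + 1/500) = 0.0775, so z = 6.02. Two-sided power at 5% is Φ(6.02 − 1.96), above 99.9%. That statement is sound and does not use the T-score cutoff.

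**The case against.** The strongest reply is that this is a slip of notation. The osteopenia range in the same cell reveals the intended direction; the symbol probably meant 2.5 or more SD below the reference, with a minus sign added. Experienced staff would probably code the usual direction. If they did not, the first frequency table would show most women as osteoporotic, with all osteopenic women among them. The primary aim names BMD rather than osteoporosis, and the Statistical Analysis section does not name the T-score category as a logistic outcome. BMD values and T-scores are themselves collected, so any category can be re-derived. The full protocol or analysis plan, not shown here, may have it right.

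Much of this stands, and it limits the consequence. Miscoding is a risk rather than an established event; the collected data, the continuous analysis and the BMD power statement are not affected. The link to the logistic model is an inference, though a close one: that section covers BMD explicitly, and Table 1 holds the only bone cutoffs.

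None of it makes the printed definition correct. A PDF-reading fault is also unlikely, since the minus signs in the neighbouring range are intact and the same inequality sign is used correctly for age at RRSO in the Statistical Analysis section.

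**Conclusion.** The concern holds. The only definition of osteoporosis in the article is reversed: it contradicts the osteopenia range beside it and leaves the lowest T-scores unclassified. This follows from the text alone.

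If the definition is applied literally, the binary outcome is the complement of osteoporosis and its odds ratio is inverted, for example 1.98 to 0.51 at assumed prevalences of 10% and 18%. The size depends on the assumed prevalences; the inversion does not, apart from any women at exactly −2.5. The damage is confined to the dichotomised osteoporosis outcome and any prevalence or logistic result built on it. Because that outcome is in the hypothesis and is a promised result, the definition should be corrected before the analysis, however likely it is that the analysts would read it as intended.

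**What to change.** In the DXA row of Table 1, define osteoporosis as T-score ≤ −2.5 and osteopenia as T-score > −2.5 and < −1. This reverses the direction, keeps −2.5 itself in the osteoporosis category as the printed symbol already does, and makes the two categories mutually exclusive.

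Confirm that the full protocol, the case report form and the derivation code, none of which is shown here, use the same rule. A cross-tabulation of the derived categories against the recorded T-scores would settle it.

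The cost is one line of text and a short code check. No new data are needed, because T-scores are already listed outcomes, and the sample size does not change. Recruitment stood at 364 of 750 in November 2020, so as of the article the correction could precede the final analysis. It also matters for the repeat BMD assessments planned every 4 to 5 years, since later analysts may take the definition from this table.
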